### Assignment of interventions

Patients deemed eligible for study participation and provided written consent will be randomly assigned to one of the three interventions, after the completion of baseline assessment. A physiotherapist, not otherwise involved in the study, will perform a computer-generated random allocation sequence (1:1:1 allocation rate) concealed in 168 consecutively numbered, opaque, sealed envelopes determining allocation to home-based telerehabilitation, home-based rehabilitation or no physical rehabilitation. Blocked randomisation will be used to achieve balanced group allocations and to ensure concealment; the block sizes will not be disclosed.

### Blinding

Before intervention allocation, baseline measures will be performed and recorded. Experienced physiotherapists, who are blinded to group allocation, will record the follow-up outcome measurements (t
_1_ + t
_2_ + t
_3_) at our outpatient facilities. The patients will be asked not to disclose any information that could give away the group allocation, and the physiotherapist will be instructed not to ask questions that could be used to identify the allocated group of the patient, before follow-up assessment has taken place.

During the following outcome assessment, a different physiotherapist will record the outcome assessment to keep the outcome assessor blinded to group allocation at all times. The patients are only blinded to the trial hypothesis in order to prevent ascertainment bias. The principal investigator will not be blinded, as he does not conduct any outcome assessments, and therefore no emergency unblinding procedure will be necessary.

### Data collection and management

The outcome assessor will record data (patient demographics, use of analgesics, walking assistant devices and possible adverse events) and obtain the HOOS or KOOS questionnaire from the patient on a standardized form during the first consultation, which will take place approximately 3–7 days after discharge. The performance-based outcome assessments will be performed thereafter and also recorded on the standardized form. This procedure will be repeated at the following follow-ups by different physiotherapists to keep outcome assessors blinded for group allocation. Four questions regarding patient satisfaction will be included in the online questionnaire before the 6-week follow-up.

All original written information and case report forms will be stored in a secured room and kept for three years after the trial completion. Electronic data will be anonymized, coded and saved on a secured server in the Capital Region of Denmark, Bornholm. A complete backup of the data entries will be performed every month until trial completion.

Exercise data from the home-based telerehabilitation will be coded and saved on a secured server in the Capital Region of Denmark. The stored data set will be coded in a way so that group allocation is concealed, allowing for blinding of the data analyst.

Participant retention and completion of follow-up assessments are expected to be relatively high due to the comprehensive follow-up assessment of this trial. While standard of care usually includes a 3 months’ follow up, patients included in this trial are invited to follow-up assessments at 6 weeks, 3 and 12 months postoperatively, which includes a free-of-charge consultation with a physiotherapist.

## Statistical methods

The main analysis plan is outlined below, while a detailed analysis can be found in our extended data
^23^.

The trial is designed to test the hypothesis that physical rehabilitation (home-based telerehabilitation and home-based rehabilitation combined) is superior to no physical rehabilitation following THA and TKA or if one of the physical rehabilitation strategies is superior to no physical rehabilitation. Superiority of physical rehabilitation over no physical rehabilitation will be claimed if the between-group contrast at the 6 weeks follow-up is 10 HOOS/KOOS ADL-subscale points or greater in favour of the physical rehabilitation. Superiority of an individual physical rehabilitation strategy over no physical rehabilitation will be claimed if the same criteria are met and in favour of that physical rehabilitation. 

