### Primary analysis

The primary analysis will evaluate the mean difference at 6 weeks follow-up between physical rehabilitation (home-based telerehabilitation and home-based rehabilitation) and no physical rehabilitation. This will be assessed by independent two-sample t-tests if normality assumptions are acceptable, otherwise the Wilcoxon sum rank-test will be used. The same tests will also be used to compare the individual physical rehabilitations to no physical rehabilitation.

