### Sample size

A clinically important difference of 10 points on the HOOS/KOOS subscale function in daily living (ADL)
^36,
45^ is used as our superiority margin, with an expected standard deviation of 20 points, a power of 0.80 and a significance level of 0.05 resulting in a sample size of 50 patients in each group. With 10% loss to follow up
^46^ this results in 56 patients in each group. This calculation will be used for each comparison of individual physical rehabilitations to no physical rehabilitation; therefore, 56 patients are needed for each of the three groups resulting in 168 patients included in total (3 groups of 56 patients). Comparison of any physical rehabilitation to no physical rehabilitation is done under the same clinically important difference and expected standard deviation as the individual comparisons. With a sample size of 100 (patients receiving one of the two physical rehabilitation strategies) and 50 (patients receiving no physical rehabilitation) the expected power is 0.89.

We expect a relatively low inclusion rate of 50%, since one of the interventions includes “no physical rehabilitation”, compared to standard rehabilitation. Furthermore, based on the expected patient flow at our trial sites and the need to conduct the trial within a realistic timeframe, we do not initially intend to stratify THA and TKA for subgroup analysis. There will not be any specific strategies for increasing participant enrolment related to this trial.

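### The 10-point rule for claiming superiority and the stated power of 0.80 and 0.89 belong to different tests: at a true difference of 10 points, each contrast meets the rule only half the time

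*Protocol article*

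**What the plan says.** In the protocol article, Statistical methods, superiority of rehabilitation over no rehabilitation "will be claimed if the between-group contrast at the 6 weeks follow-up is 10 HOOS/KOOS ADL-subscale points or greater". For each single strategy, superiority "will be claimed if the same criteria are met and in favour of that physical rehabilitation". Neither sentence mentions a p-value or a confidence limit.

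Under Primary analysis, the pooled contrast and the individual contrasts are to be tested: "This will be assessed by independent two-sample t-tests if normality assumptions are acceptable", otherwise by a rank-sum test. No shifted null value is given.

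Under Sample size, the 10-point clinically important difference "is used as our superiority margin, with an expected standard deviation of 20 points", with "a power of 0.80 and a significance level of 0.05 resulting in a sample size of 50 patients in each group". After allowing for 10% loss, "this results in 56 patients in each group". The pooled comparison "is done under the same clinically important difference and expected standard deviation as the individual comparisons", and its power with 100 vs 50 patients is given as 0.89. The sidedness of the 0.05 level is not stated, and no expected true difference larger than 10 appears anywhere.

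**The concern.** A power figure is the probability that the trial meets its own success criterion at a stated true effect. Here the criterion is an observed contrast of at least 10, and the only effect in the sample size is also 10. An unbiased, symmetric estimate falls below its true value half the time, so a criterion set at the target difference cannot have power of 0.80 or 0.89 at that difference.

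Two things are at stake. First, a reader who takes the stated power at face value will read a missed claim as stronger evidence against a 10-point benefit than it is. Second, the planned test and the claim rule can disagree on the primary contrast: a result may be significant against zero and still not count as superior. The trial asks whether rehabilitation is superior to none, and the Pragmatism section says the municipality wants an estimate of effectiveness before it invests in the technology. The meaning of a missed claim therefore matters.

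**Working it through.** **Inputs.** Difference 10, SD 20, level 0.05, power 0.80, 50 per group, 10% loss, and 100 vs 50 for the pooled contrast (all from Sample size). Claim threshold 10 (Statistical methods). Test against zero (Primary analysis; no shifted null is stated).

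**Step 1. Reproduce the plan's figures.** SE = 20 × √(1/n₁ + 1/n₂), which is 4.00 for 50 vs 50 and 3.46 for 100 vs 50.

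- One-sided 0.05, null 0, true difference 10: n = 2 × [20 × (1.645 + 0.842)/10]² = 49.5, so 50 per group. 50/0.9 = 55.6, so 56.
- Power, 50 vs 50: Φ(10/4.00 − 1.645) = Φ(0.855) = 0.80.
- Power, 100 vs 50: Φ(10/3.46 − 1.645) = Φ(1.242) = 0.89.
- Two-sided 0.05 does not reproduce them: n = 63 per group, and power is Φ(2.50 − 1.96) = 0.71 and Φ(2.89 − 1.96) = 0.82.

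The stated figures are therefore those of a one-sided 5% test against zero, with 10 as the target difference.

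**Step 2. Probability of meeting the stated rule.** P(estimate ≥ 10 | true d) = Φ((d − 10)/SE).

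- At d = 10 this is Φ(0) = 0.50 for every contrast, whatever the n, SD or allocation ratio.
- Adding two-sided p<0.05 leaves 0.50 at SD 20, because the smallest significant estimates are about 7.9 (50 vs 50) and 6.8 (100 vs 50), both below 10. One-sided, they are lower still.
- At least one of the three contrasts reaching 10, if both strategies truly differ from control by 10: about 0.67 by simulation. The reasoning agrees. If the pooled contrast reaches 10, so does at least one single contrast. The event therefore fails only when the control group's sampling error is the largest of three exchangeable errors, which has probability 1/3.

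**Step 3. The margin reading.** If a lower confidence limit must exceed 10, the probability at d = 10 is 0.025 (two-sided 95% interval) or 0.05 (one-sided). With the two-sided interval, 80% would need a true difference of 10 + (1.96 + 0.842) × SE, which is 21.2 (50 vs 50) or 19.7 (100 vs 50).

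**Step 4. True difference at which the stated rule has the stated power.**

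- Individual contrast, 80%: 10 + 0.842 × 4.00 = 13.4.
- Pooled contrast, 89%: 10 + 1.227 × 3.46 = 14.2.

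**Step 5. Where test and rule disagree.** A pooled estimate of about 7 to 9.9 is significant on the two-sided test but does not meet the rule. At a true pooled difference of 8, the rule is met with probability Φ(−2/3.46) = 0.28. The test against zero rejects with probability 0.63 two-sided, or Φ(8/3.46 − 1.645) = 0.75 on the one-sided test that matches the plan's power.

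**Step 6. False claims.** At a true difference of zero the rule is met with probability Φ(−2.50) = 0.006 (50 vs 50) and Φ(−2.89) = 0.002 (100 vs 50).

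**The case against.** The strongest reply is that requiring a clinically important difference before claiming superiority is a legitimate, strict choice. That stands. A pooled estimate of 8 that is significant but not called superior is not an error in itself. What does not stand is reporting the power of a different rule beside it.

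A second reply is that the article refers to extended data for the detailed analysis, and a significance condition may be stated there. It may, so one should not insist that the test plays no part in the claim. But such a condition can only lower the probability of a claim, and at SD 20 it leaves 0.50 unchanged. The rule and the power are both stated in full in the article.

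A third reply is that the article never calls 10 the expected true effect. That is correct; it is inferred from the reproduction in Step 1. No other difference gives the stated numbers with the stated SD, and none is offered.

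Four stronger readings are tempting and are not supported:

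- *The rule is too lenient.* It is stricter than the test; Step 6 shows very few false claims at zero effect.
- *A claim at exactly 10 is unsafe because its interval reaches down to about 3 (pooled) or 2 (individual).* That interval excludes zero, so an ordinary superiority rule would make the same claim.
- *The plan cannot answer its question because it has no basis for concluding that rehabilitation does not work.* The trial is defined as a superiority trial and plans no equivalence claim. Secondary analysis also commits to 95% confidence intervals at each endpoint, so readers can see whether 10 points is excluded.
- *The trial as a whole has a 50% chance of success.* The 0.50 is per contrast and at a true difference of exactly 10.

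**Conclusion.** The concern holds as a mismatch between the claim rule and the power statement. At the difference used to size the trial, the rule is met with probability 0.50 per contrast (about 0.67 for at least one of three), against a stated 0.80 and 0.89. No reading of the rule, whether as point estimate, point estimate with significance, or confidence limit above 10, yields the stated figures.

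The 0.50 rests only on an estimate distributed symmetrically around the true value. The significance thresholds, the 13.4 and 14.2 points, and the probabilities at a true difference of 8 also rest on the plan's SD of 20 and on 50 and 100 evaluable patients. The sample size arithmetic is not wrong in itself: it is right for a one-sided 5% test against zero. The matter should be settled before analysis because it governs the primary conclusion.

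**What to change.** Make the rule and the power refer to the same test, in one of two ways.

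(a) Keep the 10-point rule. In Sample size, state that at a true difference of 10 the probability of a claim is 0.50 per contrast, and that a true difference of about 13.4 (individual, 80%) or 14.2 (pooled, 89%) would be needed. Say that the existing 0.80 and 0.89 describe a one-sided 5% test against zero.

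(b) By a dated amendment before any unblinded analysis, base the claim on the test or confidence interval against zero, and interpret the estimate and its interval against the 10-point clinically important difference. Replace *superiority margin* with *target difference* and state the sidedness. With two-sided 5%, restate power as about 0.71 (50 vs 50) and 0.82 (100 vs 50); 0.80 and 0.89 may stay only if the test is declared one-sided at 5%. Changing the one term alone would leave the power figures wrong under a two-sided rule.

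Neither option needs more patients or data. Under (a), the stated power becomes much less favourable. Under (b) with a two-sided test, it becomes somewhat less favourable, and the observed pooled difference needed for a claim falls from 10 to about 6.8. The study status given under Dissemination policy records the last participant as recruited on 27 January 2021, so (b) relaxes a prespecified criterion after enrolment closed. The amendment and the trial report must say so.

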### Analysis outline

The primary outcome is the mean difference in the HOOS/KOOS subscale: function in daily living (ADL). Primary endpoint will be differences between groups at first follow up (t
_1_), secondary endpoints being differences at second follow-up (t
_2_) and final follow up (t
_3_) (see extended data item 3: schedule for enrolment, intervention, and outcome assessments
^23^).

Data analysis will follow the intention-to-treat principle. To allow for full data analysis, missing data will be imputed using multiple imputations.

### Primary analysis

The primary analysis will evaluate the mean difference at 6 weeks follow-up between physical rehabilitation (home-based telerehabilitation and home-based rehabilitation) and no physical rehabilitation. This will be assessed by independent two-sample t-tests if normality assumptions are acceptable, otherwise the Wilcoxon sum rank-test will be used. The same tests will also be used to compare the individual physical rehabilitations to no physical rehabilitation.

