### Eligibility criteria

In order to increase the external validity and improve the generalizability of this trial, only few eligibility criteria will be used. This will furthermore reflect current clinical practice and enhance the pragmatic nature of the trial.

Inclusion criteria:

-Patients having had primary, unilateral THA or TKA due to osteoarthritis.-Patients being referred to receive postoperative rehabilitation at our institution.-Patients being able to speak, read and understand Danish language.-Patients aged ≥ 18 years.

Exclusion criteria:

-Patients not able to comply with exercise instructions.-Patients who are discharged to a nursing-home facility or receiving in-home rehabilitation by home care.

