Like the above-mentioned subscale, these subscales are scored by the degree of difficulty the patient has experienced in the last week on a 5-point Likert scale. Each subscale provides a score, which can be calculated to a total score ranging from 0 (worst/extreme difficulties) to 100 (best/ no problems). At least 50% of the questionnaire items in each subscale are required to be answered to permit calculation of a mean score. A total score of the questionnaires has not been validated and is therefore not recommended
^36^.

*Patient global assessment.* At baseline the patient’s perception of his or her overall functional ability will be assessed using a single numeric rating scale, as recommended by OARSI
^37^. The patient will be asked a single question: “How would you rate your current level of function during your usual activities of daily living?” During follow-up assessment patients will be asked the same question as at baseline. Their answer will be rated on a 0–100 visual rating scale with end-points anchored as “Inability to perform any daily activities” (0) and “No problem with any daily activity” (100)
^37^.

*30-s chair stand test.* Performance-based assessment will be performed using the 30-s chair-stand test, which represents the
*sit-to-stand activity*. The test counts the number of sit-to-stand repetitions the patient can perform in 30 seconds. The straight-back chairs used for testing during all outcome assessments will be of the same model, same height (approximately 43 cm) and will be placed against a wall. Any other adaptations (i.e. the use of armrests or assistive devices) will be reported. To assure understanding, two slow-paced repetitions will be practiced before the test initiates. The 30-s chair stand test has proven good reliability to measure functional performance following THA and TKA
^43,
44^.

*40 meters walking test.* This performance-based assessment measures short distance walking activity. The patient will be instructed to walk as quickly as safely possible to a mark 10 meters away, return and repeat for a total distance of 40 meters. Each walk of 10 meters (excluding the turn time) is recorded and expressed as speed m/s by dividing distance by time in seconds. A practice walk up and back will be performed to assure understanding. Any assistive devices used will be recorded.

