### Secondary analysis

The secondary analysis will test differences in the mean score of all continuous secondary outcomes at the primary, secondary and final endpoints and will be performed in the same way as the primary analysis. Nominal outcomes will be analysed by the chi-squared test or in cases with less than five expected counts for any observation, Fishers exact test will be used.

At baseline descriptive statistics will be presented. At each endpoint, mean scores, standard deviations, between-groups mean (with corresponding 95% confidence intervals) and p-values will be reported (see extended data item 4: analysis outline for primary and secondary analysis
^23^).

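### Unadjusted tests for the primary and continuous secondary outcomes leave joint type, age and baseline function unused: valid, but an avoidable loss of precision

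*Protocol article*

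**What the plan says.** - **Primary analysis:** "This will be assessed by independent two-sample t-tests", with the Wilcoxon rank-sum test as the fallback if normality is not acceptable. The same tests compare each rehabilitation arm with no rehabilitation. No covariate or stratum is named.
- **Secondary analysis:** the analysis of continuous outcomes "will be performed in the same way as the primary analysis". For the rest, "Nominal outcomes will be analysed by the chi-squared test", or Fisher's exact test where expected counts are small.
- **Eligibility criteria:** both operations are admitted: "Patients having had primary, unilateral THA or TKA due to osteoarthritis". Hips are scored on HOOS and knees on KOOS, and the two are analysed as one outcome.
- **Assignment of interventions:** "Blocked randomisation will be used to achieve balanced group allocations and to ensure concealment". The ratio is 1:1:1, from 168 consecutively numbered envelopes. No stratification factor is mentioned.
- **Sample size:** for reasons of patient flow and timeframe, "we do not initially intend to stratify THA and TKA for subgroup analysis".
- **Baseline data taken before allocation:** under Elaborated description of outcome measures, the patient's "overall functional ability will be assessed using a single numeric rating scale" at baseline. Under Data collection and management, HOOS/KOOS and the performance tests (30-s chair stand, 40 m walk) are recorded at the first consultation.
- **Outcomes:** a change score is rejected because the authors consider that no valid ADL subscale score can be obtained before 6 weeks after surgery.
- **Additional analyses:** age is said to be able to affect the results, and an exploratory age subgroup analysis is planned. Imputation models draw on all other available variables.

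**The concern.** Two operations, scored on two instruments, go into one mean per arm, and neither the randomisation as described nor the analysis takes account of joint type. Whatever variance in 6-week ADL is explained by joint, age and early function stays in the error term, although all of these are known before allocation.

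The reasons the article gives do not cover this choice. The objection to an early ADL score concerns that one subscale, and concerns a change score. It says nothing about joint type, age, walking speed or the chair stand. The patient-flow argument concerns subgroup analysis, whereas a covariate needs no extra patients. For the chair stand, the walk and the global rating, the same variable exists at baseline and is not used in the comparison. Baseline data inform the imputed values but not the treatment contrast.

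At stake are the width of the confidence interval and the power of the comparisons. The estimate could also be moved by a chance difference in case mix, in a trial that claims superiority on a contrast of at least 10 points.

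**Working it through.** **Inputs from the article (Sample size):** difference 10, SD 20, significance level 0.05 with sidedness not stated, power 0.80, 50 per group (56 after 10% loss), and power 0.89 for 100 versus 50.

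**Assumed, because the article does not give them:** covariate R² of 0.04, 0.10, 0.20 and 0.30; a THA–TKA difference in mean 6-week ADL of 5, 10 or 15 points; a 50/50 joint mix.

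**Step 1. Reproduce the plan's figures (no covariates).** The standard error is 20 × √(1/50 + 1/50) = 4.00 for a pairwise contrast and 20 × √(1/50 + 1/100) = 3.46 for the pooled contrast. The noncentrality is 10/4.00 = 2.50 and 10/3.46 = 2.89. Noncentral-t power:

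- One-sided 0.05: 0.799 pairwise and 0.890 pooled. By the normal approximation n is 50 per group, and 50/0.9 rounds up to 56. All the stated figures reproduce.
- Two-sided 0.05: 0.697 pairwise and 0.818 pooled, with 63 per group needed. The stated figures do not reproduce.

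Both readings are carried forward.

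**Step 2. Effect of adjustment.** Residual SD = 20 × √(1 − R²), put into the same formula. The few degrees of freedom spent on covariates are ignored.

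| R² | Residual SD | 50 v 50, one-sided | 50 v 50, two-sided | 100 v 50, one-sided | 100 v 50, two-sided |
|---|---|---|---|---|---|
| 0 | 20.00 | 0.799 | 0.697 | 0.890 | 0.818 |
| 0.04 | 19.60 | 0.813 | 0.714 | 0.901 | 0.833 |
| 0.10 | 18.97 | 0.835 | 0.742 | 0.917 | 0.856 |
| 0.20 | 17.89 | 0.871 | 0.790 | 0.942 | 0.894 |
| 0.30 | 16.73 | 0.907 | 0.841 | 0.963 | 0.929 |

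The equivalent gain in sample size is 1/(1 − R²): 4%, 11%, 25% and 43% more patients.

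**Step 3. Joint type alone.** With a 50/50 mix, R² = 0.25 × D²/400. For D = 5, 10 and 15 this is 1.6%, 6.3% and 14.1%.

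**Step 4. Chance imbalance.** The SD of the difference in THA share between two arms of 50 is √(0.25 × 2/50) = 0.10, so the 95% range is about ±20 percentage points. The contrast then shifts by 0.196 × D, or about 1, 2 or 3 points for D = 5, 10 or 15. With D = 10, a 1-SD imbalance moves it by 1 point, a quarter of the standard error of 4.00.

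**The case against.** The strongest reply is that nothing here is wrong. A two-sample t-test in a randomised trial is unbiased with valid type I error, and the sample size was worked out for that test with no allowance for covariates. Chance imbalance in joint type is already part of the standard error. This stands, and it limits the point to efficiency. A reader might infer that pooling hips and knees, or a chance THA/TKA imbalance, biases or invalidates the primary result. The documents do not support that.

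A reader might also infer that the trial has only 0.70 power and that covariates are needed to repair it. The 0.70 comes from a two-sided reading. The article does not state sidedness, and its own figures fit one-sided 0.05. That is a separate question.

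Other points that stand:

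- The R² range is assumed. Baseline is usually 5 to 7 days after surgery and may predict weakly. At R² 0.04, two-sided pairwise power moves only from 0.697 to 0.714.
- The global rating asks about usual daily activities, so part of the article's doubt about early ADL scores may extend to it. Walking speed and joint type are not open to that doubt.
- The article's superiority rule is an observed contrast of at least 10 points. Read literally, with a true difference of 10, it is met about half the time whatever the residual SD. The power gains apply to the significance test and the interval, not to that rule.
- The article does not say outright that randomisation was unstratified. A single list is an inference from the numbered envelopes. The sentence about not stratifying THA and TKA concerns subgroup analysis only.
- More detailed analysis is said to be in extended data that are not shown, so the absence of an adjusted sensitivity analysis there cannot be claimed. The article itself nevertheless commits the main analysis to unadjusted tests.

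**Conclusion.** The point holds as an avoidable loss of precision, with no adjustment for chance imbalance, in an otherwise valid analysis. Over the assumed R² of 0.04 to 0.30, pairwise power at 50 versus 50 would rise by about 1 to 11 percentage points at one-sided 0.05, and by about 2 to 14 at two-sided 0.05. Chance imbalance in joint type could move a pairwise contrast by roughly 1 to 3 points at the edge of its 95% range, if hips and knees differ by 5 to 15 points. None of these R² values or joint differences comes from the article, and at the low end the benefit is small. The case is firmest for the continuous secondary outcomes that have their own baseline value, because there the natural covariate is already recorded and no stated reason excludes it.

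**What to change.** In a dated amendment, made before the analyst is unblinded:

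- **Primary outcome:** a linear model (ANCOVA) of 6-week HOOS/KOOS ADL on arm, with joint type, age and a baseline function measure (40 m walking speed, the global rating, or both) named in advance. Report the adjusted mean difference with its 95% confidence interval.
- **Continuous secondary outcomes with a baseline value:** adjust for that value and for joint type.
- **Sensitivity analysis:** keep the planned t-test, with its Wilcoxon fallback, unadjusted.

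An exploratory arm-by-joint interaction could be added, but it is a matter of preference and not needed for this point.

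The cost is small but not nil. The covariates are already collected and no further patients are needed. However, the article reports that participant 168 was recruited on 27 January 2021 and lists no amendments. The primary analysis would therefore change after recruitment closed, and the amendment must show its date and that the analyst was still blinded. The gain may also prove modest if the covariates predict weakly.
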